### 9.3 Qualitative Measures

In the subsequent years when HTC services will be offered in study communities and HTC uptake will be measured, in-depth semi-structured interviews will be conducted in a random sample of HIV-negative men who tested initially (at baseline, when incentives were offered), and then either continued to test in subsequent years (N = about 10-20) or did not test (N = about 10-20). Interviews will assess the long-term influence of incentives on men's attitudes towards HIV testing. Procedures followed in the in-depth interviews will be similar to those used at baseline, in the incentives trial.

### 9.4 Analysis

*Long-term effects of incentives:* We will examine trends in HTC uptake over a period of up to 36 months for the individuals who participate in the incentives trial. To control for time trends in HTC uptake that may bias our results, we will also utilize longitudinal data on HTC uptake by men in the SEARCH Trial communities. We will assess whether HTC uptake is maintained at baseline levels or if instead it declines over time at rates that exceed what is observed in the SEARCH Trial among men who test at baseline.

*Cost-effectiveness:* We will conduct five linked analyses. In each we will compare among incentive arms and to non-incentive SEARCH communities. (1) Increased short-term testing: cost per added person tested and HIV-infected person identified. (2) Increased HIV treatment: cost per added person with HIV RNA suppression (i.e., tested and achieved or maintained virologic suppression). (3) Reduced disease burden: cost per averted disability-adjusted life year (DALY) based on improved testing and treatment (with higher and earlier initiation of ART). This will include modeled lifetime ART health benefits and costs. (4) Repetition of analyses 1-3 incorporating the long-term (3 year) effects of incentives on testing (as assessed in this 3rd Aim). If the proportion of participants testing at future HTC campaigns remains similar to the proportion who tested when incentives were offered, the increased yield of testing and HIV-infected individuals identified in those future years – with no added incentive cost – will result in more favorable cost-effectiveness ratios. (5) Cost implications of incentives given a community target testing level. Increased HTC uptake at mobile venues due to incentives (and thus decreased need for resource-intensive tracking and testing) could generate overall cost reductions for identifying persons unaware of their infection. The main outcome metric will be how many additional high-risk men can be tested by spending fixed resources on novel rather than standard incentives. These analyses will be conducted using customized spreadsheet-based decision tree and clinical progression simulation modeling methods adapted from our past projects. Extensive 1-way, multi-way, threshold, and scenario sensitivity analyses will quantify the effects of input uncertainty on results. Our analytic perspective will be the health system, for direct medical costs, discounting future costs and DALYs at 3% per year.

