**Aim 4. Assess the sustainability of providing incentives for HTC and the cost-effectiveness of novel incentive strategies for HTC and HIV virologic suppression.** We will examine the extent to which incentives in one year (Aim 1) affects participation in subsequent testing efforts without incentives. We will also assess effects of the Aim 2 intervention on viral suppression 6 months after incentives are discontinued, i.e. at 12 months. This will reveal whether incentives increase or decrease men's motivation for future HIV testing. We

will also calculate the incremental cost of incentives per additional person tested and enrolled in care as well as the cost per disability-adjusted life year (DALY) averted.

Our overall objective is to generate evidence on how best to use low-cost incentives to promote HIV testing among adult men and maximize the benefits of ART among HIV-infected adults in rural Uganda, and to critically evaluate the sustainability of such an intervention.

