### 5.2 Randomization

We will compare two theoretically motivated incentive interventions to a standard, fixed incentive intervention. Each intervention will seek to encourage HTC uptake at testing venues in the community (described below).

The incentive interventions will have up to three different values in order to inform researchers and policymakers about the optimal incentive size. The *expected value* of each incentive intervention, within each tier of incentive value, will be the same so that we can draw unambiguous conclusions about the reasons why some incentive interventions work better than others. We will select up to three tiers of incentive value (e.g. low, medium and higher value incentive values), with the specific amounts of expected values per person in US dollars for the incentives determined during pre-enrollment community advisory board meetings. The expected value of the *highest* tier of incentive value will not exceed \$10/person, an amount that resembles

what has been used in some other studies in the region [27, 51], and that also corresponds to the sum of transport costs and the opportunity costs of time for some segments of the population.

Study participants will be randomized in equal ratios to the three incentive strategies and to up to three tiers of incentive value, as described below. Randomization will be performed with computer-generated assignments that are grouped in blocks so as to ensure roughly equal sizes in each study group.

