## 9.0 Sustainability & Cost-Effectiveness

Repeat HIV testing among high-risk individuals is essential for the success of combination HIV prevention. By engaging men in first-time testing as part of our HIV testing incentives trial (Section 5), there may be an important opportunity for establishing healthy behaviors. To examine issues related to the sustainability of offering incentives and the cost-effectiveness of such an approach, we will quantitatively and qualitatively assess *repeat* testing behavior among participants in the study communities where we conduct the incentives trial. We will thereby address an important question that has rarely been examined: do one-time incentives strengthen or weaken individuals' likelihood of testing routinely once incentives are no longer offered? We will also address a central policy issue: the cost-effectiveness of using incentives to promote HTC and HIV treatment.

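### Section 9.4 reads Aim 4 sustainability from the fall below the incentivised Aim 1 round; short of full maintenance, this measures retention of the paid level, not whether incentives strengthened or weakened later testing

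*Protocol*

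**What the plan says.** The question is put in section 9.0: "do one-time incentives strengthen or weaken individuals' likelihood of testing routinely once incentives are no longer offered". The Aim 4 text in section 2 promises an answer: "This will reveal whether incentives increase or decrease men's motivation for future HIV testing".

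The long-term effects paragraph of section 9.4 says how this will be judged: "We will assess whether HTC uptake is maintained at baseline levels or if instead it declines over time at rates that exceed what is observed". The benchmark is SEARCH men who tested at baseline. The purpose given for the SEARCH data is limited: "To control for time trends in HTC uptake that may bias our results, we will also utilize longitudinal data on HTC uptake by men" (SEARCH communities are meant).

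Four other places fix what this means.

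- Section 9.3 describes the Aim 1 baseline when it selects men "who tested initially (at baseline, when incentives were offered").
- Section 5.2 has no zero-incentive arm: "Study participants will be randomized in equal ratios to the three incentive strategies and to up to three tiers of incentive value".
- Section 9.1 reduces or drops the incentive in the later rounds.
- Table 1 lists uptake 1 and 2 years after the incentives as an Aim 4 outcome, which is a level and not a change.

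The cost-effectiveness paragraph of 9.4 also says: "In each we will compare among incentive arms and to non-incentive SEARCH communities".

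**The concern.** The starting level on the Aim 1 side contains the immediate response to the incentive. That response can vanish when payment stops, even if men's willingness to test unpaid is unchanged or improved. SEARCH can remove a time trend. A comparator that was never paid cannot remove the loss of a payment. A fall steeper than in SEARCH is therefore expected under a modest lasting gain, under no lasting effect and under crowding-out.

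The risk is one of interpretation. A one-time incentive with a real but partial lasting benefit could be called unsustainable, or could be said to have weakened motivation, on evidence that does not separate these cases. The contrast that randomisation protects, follow-up uptake between incentive types and value tiers, is not mentioned in this paragraph.

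**Working it through.** The protocol gives no threshold, margin or power for this analysis, so there is no stated figure to reproduce.

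**1. What the comparison estimates**

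Let U0 and U1 be uptake without any incentive at baseline and at follow-up, B the initial boost from the incentive, and L the lasting effect once it is withdrawn.

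- Aim 1 paid round: U0 + B
- Aim 1 follow-up, unpaid: U1 + L
- Aim 1 change: (U1 - U0) + L - B
- Comparator change, no incentive and same trend: U1 - U0
- Excess change: **L - B**

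The trend cancels and the boost does not. The excess is negative whenever L is below B, whatever the sign of L. If a reduced incentive still adds R at follow-up, the excess is L + R - B, which mixes in one more component.

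**2. Numbers**

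The paid-round rates of 50% (lottery) and 40% (fixed) are planning assumptions in section 5.7.3. The no-incentive rate of 30%, taken as flat, is assumed here.

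| Paid round | Lasting effect | Follow-up | Aim 1 change | Comparator change |
|---|---|---|---|---|
| 50% | +5 | 35% | -15 | 0 |
| 50% | 0 | 30% | -20 | 0 |
| 50% | -5 | 25% | -25 | 0 |
| 40% | +5 | 35% | -5 | 0 |
| 40% | +10 | 40% | 0 | 0 |

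Only the last row, where the lasting effect equals the whole boost, shows no excess decline. With a paid round of 50%, no-incentive uptake of 20% to 35%, a comparator trend of 0 or -5 points, and lasting effects of -5 to +10 points, every combination shows excess decline. Reading the rate of decline proportionally does not help. At 50% paid, 30% unpaid, a trend of -5 and a lasting effect of +5, follow-up is 30%. That is a relative fall of 20/50 = 40%, against 5/30 = 17% in the comparator.

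**3. Both sides restricted to baseline testers**

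The benchmark is worded "declines over time at rates that exceed what is observed in the SEARCH Trial among men who test at baseline", so a testers-only reading is possible. Assume 30% of men would test anyway and retest at 70%, while a further 20% came only for the incentive and retest at 20%.

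- Aim 1 testers: (0.30 x 0.70 + 0.20 x 0.20) / 0.50 = 0.25 / 0.50 = 50%
- SEARCH testers: 70%

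The lasting effect in the men drawn in is their 20% minus what the same men would have done without the earlier incentive. That second quantity appears nowhere in the comparison, so 50% against 70% fits a gain, no effect or a loss.

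**4. Illustration of precision**

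Assume 3,000 men per side, unpaid uptake of 30% with no trend, independent rounds, and excess decline declared at z < -1.96. This test is an assumption and is not in the protocol.

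- Boost 15, lasting +7.5: SE = sqrt[(0.45 x 0.55 + 0.375 x 0.625 + 2 x 0.30 x 0.70) / 3,000] = 1.73 points. Then z = -7.5 / 1.73 = -4.33, and the probability of declaring excess decline is 0.99.
- Boost 10, lasting +5: SE = 1.72 points, z = -2.91, probability 0.83.
- Testers only, boost 15, retest rates 70% and 50%: Aim 1 retention is (0.21 + 0.075) / 0.45 = 63.3% against 70%. With 1,350 and 900 testers, SE = 2.01 points, z = -3.31, probability 0.91.

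**The case against.** **Retention is a legitimate quantity.** Section 9.1 gives the objective as durability of the initial effect, and the share of the paid level that survives bears on that. Uptake fully held without payment would indicate a lasting gain. Both points stand, so a reader should not infer that the comparison is uninformative. It fails for the strengthen-or-weaken question when uptake falls by more than the comparator.

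**No decision rule is stated.** The paragraph speaks of examining trends and assessing decline, and falls of 15, 20 and 25 points are different results. This also stands: a reader might infer a pass-or-fail test, and the protocol contains none. But the three falls can be told apart only by someone who knows the boost, and with no zero-incentive arm the trial does not measure it.

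**Arm comparisons and follow-up levels are not wholly absent.** The cost-effectiveness paragraph compares among arms, its fourth analysis brings in 3-year testing effects, and Table 1 lists follow-up uptake. It would therefore be wrong to say that section 9.4 has no long-term arm comparison, or that the cost-effectiveness work must rest on the decline sentence. The gap is in the long-term effects paragraph: no comparison of testing uptake by arm or tier is planned there.

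**SEARCH as a no-incentive comparator.** This is stated for the cost-effectiveness analyses and is assumed here to hold for the long-term paragraph too.

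**Comparing follow-up levels with SEARCH is no clean substitute.** Section 3.1 draws the Aim 1 communities from those not enrolled in SEARCH, and a change comparison adjusts for fixed differences between communities. With 3,000 men per side and uptake of 35% against 30%, a level test has SE = 1.21 points and z = 4.14. A fixed 5-point community difference would then be mistaken for a lasting effect about 99% of the time. This stands, and the level comparison can only be supportive.

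**Conclusion.** The concern holds for the long-term effects paragraph of section 9.4. Decline from the incentivised round, net of a no-incentive comparator, equals the lasting effect minus the initial boost. It cannot answer the question in sections 2 and 9.0 for any lasting effect smaller than the boost. That result is algebra. It needs only a comparator without incentives, a shared trend and unpaid follow-up; a reduced incentive at follow-up adds a further component. The 30% no-incentive uptake, the retest rates, the 3,000 SEARCH men and the z threshold are assumptions. The probabilities built on them are illustrations and do not describe a planned test.

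A reader might go further and conclude that Aim 4 can be made to show the effect against no incentive by rewording the analysis. The documents do not support that. Aim 1 has no zero-incentive arm, so randomised contrasts give relative durability only, and anything against SEARCH is non-randomised. The change is still worth making, because it alters what Aim 4 may conclude.

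**What to change.** Amend the long-term effects paragraph of section 9.4.

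1. Make the main analysis a comparison of testing uptake in each follow-up round among all randomised Aim 1 men, as assigned, between incentive types and between value tiers. State that it shows relative durability and not the effect against no incentive. Record any reduced incentive offered in a later round, by original arm, so that the contrast can be read as an effect of the earlier incentive.
2. State that decline from the incentivised round, with or without the SEARCH adjustment, measures retention of the paid level and will not be interpreted as weakened or strengthened later testing.
3. Optionally, report the follow-up level against the SEARCH level at the same time, in men not selected on earlier testing. Label it supportive and non-randomised, place it beside the change comparison and not in its stead, and note its exposure to differences between communities.

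Items 1 and 2 change wording only and use data already planned for collection; item 3 needs SEARCH uptake data on men not selected on earlier testing. The price is a narrower claim: the as-randomised contrasts can rank incentives by durability, but cannot show whether any of them beats never having offered one.

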| Aim 3 - Pilot | About 120 high risk, HIV-negative adults.                                                | Randomized trial
1. Loss-framed incentive (with or without endowment) for repeat test
2. Gain framed incentive for repeat testing
2. No incentive for repeat testing | 1. Feasibility and acceptability of loss aversion delivery strategies
2. Comparative uptake of repeat HIV testing                       |
| Aim 3 - Trial | About 525 high risk, HIV-negative adults                                                 | Randomized trial
1. Loss-framed incentive for retesting for HIV
2. Gain framed incentive for retesting for HIV
2. No incentive for retesting for HIV                 | 1. HIV retesting uptake at both 3 and 6 months following randomization                                                                     |
| Aim 4         | Same as Aim 1 study population                                                           | 1. Measurement of Aim 1 participants' HIV testing behavior in subsequent years without incentives
2. Cost-effectiveness analyses                                                         | 1. Uptake of HIV testing 1 and 2 years after use of incentives
2. Cost per added person testing and linking to care, & per averted DALY |

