#### 3.2 Study Population

Adult ( $\geq 18$  year old) men from up to four candidate study communities will be enumerated and enrolled in the Aim 1 study if they meet eligibility criteria. In Aim 2, men and women who test HIV-positive will be enrolled in the treatment incentives trial. In the Aim 3 Pilot, men and women who are HIV-negative and considered at high-risk of HIV infection will be enrolled in the pilot trial. In the Aim 3 trial (following the Aim 3 Pilot), men and women ( $\geq 18$  years old and  $<60$  years of age) who are HIV-negative, recruited at high-risk venues in southwestern Uganda, and considered at high-risk of HIV infection will be enrolled. In our Aim 4 activities, we will conduct longitudinal follow-up of the HIV testing behavior of men enrolled in Aim 1.

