### 9.1 Longitudinal HIV Testing

In each of the study communities where the incentive trial was conducted, we will measure HTC uptake at multiple time periods after the start of the incentives trial. The time periods during which we will measure HTC uptake will range from about 12-36 months after the start of the trial so that we can monitor repeat testing period longitudinally. HTC uptake will be recorded at similar HTC venues as those used at baseline, in the incentives trial. All participants will once again receive information on when and where to find the testing venues. In these subsequent time periods, incentives offered for HTC will either be significantly smaller or non-existent, since the objective will be test the durability and sustainability of the effect of offering incentives for HTC initially. As in the incentives trial conducted at baseline, we will use electronic fingerprint biometric measurements that link participants in real-time to a study ID at the time of HIV testing to determine whether study participants HIV tested or not.

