We will conduct five linked analyses. In each we will compare among incentive arms and to non-incentive SEARCH communities. (1) *Increased short-term testing:* cost per added person tested and HIV-infected person identified. (2) *Increased HIV virologic suppression:* cost per added person with virologic suppression (i.e., tested and on treatment). (3) *Reduced disease burden:* cost per averted DALY based on improved testing and treatment. This will include modeled lifetime ART health benefits and costs. (4) *Repetition of analyses 1-3 incorporating the long-term (3 year) effects of incentives* on testing (as assessed in this 3rd Aim). If the proportion of participants testing at future HTC campaigns remains similar to the proportion who tested when incentives were offered, the increased yield of testing and HIV-infected individuals identified in those future years – with **no** added incentive cost – will result in more favorable cost-effectiveness ratios. (5) *Cost implications of incentives given a community target testing level.* Increased HTC uptake at mobile venues due to incentives (and thus decreased need for resource-intensive tracking and testing) could generate overall cost *reductions* for identifying persons unaware of their infection. The main outcome metric will be how many additional high-risk men can be tested by spending fixed resources on novel rather than standard incentives.

These analyses will be conducted using customized spreadsheet-based decision tree and clinical progression simulation modeling methods adapted from our past projects [61-63]. Extensive 1-way, multi-way, threshold, and scenario sensitivity analyses will quantify the effects of input uncertainty on results. Our analytic

perspective will be the health system, for direct medical costs, discounting future costs and DALYs at 3% per year.

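### Section 9.4 judges the decline in testing among all Aim 1 men against SEARCH men selected for having tested at baseline, which biases the comparison towards finding no excess decline

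*Protocol*

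**What the plan says.** Section 9.4 of the Protocol sets the Aim 1 side of the comparison: "We will examine trends in HTC uptake over a period of up to 36 months for the individuals who participate in the incentives trial". Other sections confirm that this means everyone enrolled, whether or not they tested:

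- Table 1 (Section 1.1) gives the Aim 4 population as "Same as Aim 1 study population".
- Section 3.2 says "we will conduct longitudinal follow-up of the HIV testing behavior of men enrolled in Aim 1".
- Section 9.2 uses participants as the denominator of later uptake: "If the proportion of participants testing at future HTC campaigns remains similar to the proportion who tested when incentives were offered".

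SEARCH data are brought in for a stated purpose: "To control for time trends in HTC uptake that may bias our results". The assessment then has two limbs. The first is internal: "We will assess whether HTC uptake is maintained at baseline levels". The second is the SEARCH benchmark, namely whether uptake "declines over time at rates that exceed what is observed in the SEARCH Trial among men who test at baseline". On measurement times, Section 9.1 says "we will measure HTC uptake at multiple time periods after the start of the incentives trial". Section 9.4 does not say whether decline is absolute or relative, or from which round it is counted.

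**The concern.** A group chosen because its members tested at one round has 100% uptake at that round by definition. Its later uptake can only stay level or drop, and part of the drop comes from the selection alone. The Aim 1 cohort is not selected in this way. It starts at whatever uptake the incentives produce, so it has no built-in fall. A benchmark meant to remove time trends thus carries a fall that is not a time trend.

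This matters because later testing uptake is a listed primary outcome of Aim 4 and Section 9.0 asks whether one-time incentives strengthen or weaken routine testing. All Aim 1 arms receive an incentive, so SEARCH is the only non-incentive reference for that question.

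**Working it through.** The protocol states no decline, power or sample size for Aim 4, so there is no figure to reproduce. The check asks what the benchmark would show if there were no time trend.

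**Inputs**

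- Aim 1 baseline uptake p0: the planning values in Section 5.7.3 are 30% and 40% with fixed incentives and 50% with lottery.
- Uptake q once incentives are withdrawn: assumed. If q is what these men would do without any incentive, a fall from p0 to q is a complete loss of the incentive effect.
- SEARCH retest rate r among baseline testers: not in the document, so left free.

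**Formulas**, with decline counted from baseline

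- Benchmark fall = 1 − r. Absolute and relative falls coincide because the start is 100%.
- Aim 1 absolute fall = p0 − q, which exceeds the benchmark only if r > 1 − (p0 − q).
- Aim 1 relative fall = 1 − q/p0, which exceeds the benchmark only if r > q/p0.

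**Results**

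| Aim 1 fall | Absolute | Relative | Exceeds benchmark, absolute scale | Exceeds benchmark, relative scale |
|---|---|---|---|---|
| 40% to 30% | 10 points | 25% | r > 0.90 | r > 0.75 |
| 50% to 40% | 10 points | 20% | r > 0.90 | r > 0.80 |
| 40% to 20% | 20 points | 50% | r > 0.80 | r > 0.50 |

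Aim 1 cannot fall by more than p0 points. On the absolute scale, even a fall to zero would pass if r is below 1 − p0, that is, below 0.70, 0.60 or 0.50 for baseline uptake of 30%, 40% or 50%.

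**Plausible range of the built-in fall.** Suppose SEARCH men have constant uptake q and within-man correlation rho between rounds. Then r = q + rho(1 − q).

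- With q = 0.30, rho = 0 gives r = 0.30 and a fall of 70 points. With rho = 0.8, r = 0.30 + 0.8 × 0.70 = 0.86 and the fall is 14 points.
- With q = 0.20, the same range of rho gives falls of 80 to 16 points.

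For the 40% to 30% case (q = 0.30), r > 0.90 needs rho > (0.90 − 0.30)/0.70 = 0.86, and r > 0.75 needs rho > (0.75 − 0.30)/0.70 = 0.64.

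**Matched denominators.** A beta-binomial simulation with q = 0.30 and rho = 0.4 gave 30.0% at both rounds among all men, a fall of 0 points. Among baseline testers, uptake went from 100% to 58%, a fall of 42 points with no true change. Against the all-men benchmark, an Aim 1 fall from 40% to 30% shows as 10 points of excess decline.

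**The case against.** **Section 9.4 may be shorthand for testers against testers.** Section 9 is framed around repeat testing, which presupposes a first test. But uptake among baseline testers is 100% at baseline, so asking whether it stays at baseline level would make little sense. Section 9.3 also names men who tested initially when it means them. If the narrower reading is intended, Section 9.4 needs to say so.

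**The outcome is not fixed by the text.** This stands. A reader might infer that the incentive effect will look sustained even when it is not. The documents do not support that, for three reasons:

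- The limb on baseline levels does not use SEARCH and would register a fall, although it does not control for time trends.
- The scale matters. With r = 0.70, an Aim 1 fall from 40% to 10% is 30 points and does not exceed the benchmark's 30 points. In relative terms it is 75% against 30% and clearly does.
- If decline were compared only across the later rounds, the drop from 100% would not be counted.

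**Cost-effectiveness.** A reader might also infer that the bias carries into the 3-year repeat of the cost-effectiveness analyses. That is not stated. The text there compares later uptake with uptake under incentives and does not mention the decline benchmark. Section 9.2 uses a different SEARCH subset, men who had not tested at baseline, for a different question; that is not in itself an error.

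**Conclusion.** The concern holds as a mismatch of denominators with a known direction of bias. Counted from baseline, the benchmark includes a selection fall of 1 − r, which is never negative, so the comparison leans towards no excess decline. It can hide a complete loss of the incentive effect: a fall from 40% to 30% passes unless r exceeds 0.90 (absolute) or 0.75 (relative).

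These figures assume no time trend, decline counted from baseline, and the stated values of p0 and q. The SEARCH retest rate is unknown from the document. With moderate or high r, a large relative fall would still be detected. The supported conclusion is therefore a bias that can mislead, not a false finding that is certain.

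Leaving the scale and starting round to an analysis plan would be ordinary. The comparator, however, is fixed in the protocol, and it does not serve the purpose given for it.

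**What to change.** In Section 9.4, use the same denominator on both sides, by one of two routes:

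- all enrolled Aim 1 men against all comparable adult men in the SEARCH communities, whatever their baseline testing; or
- Aim 1 baseline testers against SEARCH baseline testers.

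The first is preferable, because men drawn to test by an incentive may differ from men who tested in SEARCH without one. Keep the Aim 1 side as the enrolled cohort; replacing it with all enumerated men would change the population under study. State whether decline is absolute or relative and from which round it is counted.

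Later-round uptake by randomised arm and value tier can be reported alongside. It cannot replace the SEARCH reference: with no arm free of incentives, it can only rank incentive types and amounts.

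The cost is a change of wording, using SEARCH data the protocol already plans to draw on, with no new participants or visits. The downside is a less lenient benchmark and, if the second route is taken, the possible difference between the two groups of testers.
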